In addition, there is no established protocol that exists for rPMS therapy, and the most effective stimulation count of rPMS per day for functional recovery from stroke is still unknown. With regard to the stimulation frequency, previous neurophysiological and clinical studies have shown that 20 to 30 Hz of rPMS therapy is effective.^[9–10,14–17]^ On the contrary, there are various reports on the total number of rPMS stimuli per day to produce a treatment effect, ranging from 1200 to 16,000.^[9–13]^ In a case–control study focusing on upper limb paralysis, the usefulness of rPMS therapy with a daily total stimulus delivery of 5000 was reported.^[14]^ However, there has been no data reported regarding the dose–response of rPMS therapy.

Therefore, we decided to examine the dose–response of daily total stimulus delivery in rPMS therapy in the treatment of upper limb paralysis secondary to stroke. The purpose of this RCT is to clarify this dose–response when combined with intensive OT in chronic stroke patients with moderate to severe upper limb hemiparesis, comparing three parallel groups. In addition, we aimed to assess the safety of rPMS therapy by comparing the incident rate of adverse events (AE) among groups.

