### Study procedure

2.4

Eligible patients who provide written informed consent will be randomly assigned at a ratio of 1:2:2 to the control group, the group receiving 2400 daily pulses of rPMS (2400 pulses group), or the group receiving 4800 daily pulses of rPMS (4800 pulses group), respectively. Patients will be randomly assigned using a computer-generated list of random numbers using blocked randomization, and stratified by the Fugl Meyer Assessment (FMA) (<20 or ≥20) and age (<65 or ≥65 years’ old). The study researcher will report to the allocator by phone, and the assignment will then be reported to the investigator. The block sizes will not be disclosed to ensure allocation concealment. rPMS therapy and intensive OT will be initiated from the day after admission (Day 1). The evaluation will be conducted on Day 14, after 2 weeks of therapy. After the evaluation, the therapy will be repeated for another 2 weeks (Day 15–28). For the control group, 4800 pulses of rPMS therapy will be performed for relief measures after the evaluation (Day 14). Another evaluation will be conducted 2 weeks after therapy (Day 28). Patients will be discharged on Day 28, after a total of 4 weeks of admission. In addition, the immediate effect of rPMS therapy will be assessed at the time of admission and the first session of rPMS therapy. We will check the long-term effect and safety of the rPMS therapy four weeks after discharge. The study flow chart is shown in Figure 1.

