To assess any muscular injury induced by rPMS therapy, laboratory tests for serum aspartate aminotransferase (AST), lactate dehydrogenase (LDH), and creatine kinase (CK) will be serially checked.

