### Sample size estimation

2.10

The target sample size for this randomized trial is 50. This number is based on the results of a previous case–control study in subacute stroke by Yang et al, which compared the improvement of FMA changes between patients who received both rPMS therapy in the shoulder muscles and rehabilitation therapy (treatment group), and the patients who received both NMES therapy and rehabilitation (control group). This study revealed that the FMA score in the rPMS and control groups improved by 11.47 ± 2.72 and 5.40 ± 1.80 (mean ± standard deviation), respectively.^[14]^ Occupational therapy alone has been shown to improve FMA scores by 3.4 in the chronic phase of stroke.^[25]^ Based on these reports, we predicted that a therapeutic effect of the intervention for chronic stroke may occur at a 65% of that for subacute stroke. In addition, we predicted that the therapeutic effect in the group receiving 2400 pulses of rPMS will occur at 50% of those receiving 4800 rPMS in therapy. The estimated changes in the FMA scores of the control group, 2400 pulses group, and 4800 pulses group are therefore 3.4, 5.4, and 7.4, respectively, and the assumed standard deviation is 3. A sample size of 8 patients in the control group, 16 patients in the 2400 pulses group, and 16 in the 4800 pulses group will provide an 80% power to detect differences of the change in FMA among the groups, using the maximum contrast method with contrast coefficients (−1, 0, 1), (−1, −1, 2), (−2, 1, 1) at a 5% level of significance (2-sided). A dropout rate of 20% is allowed. A total sample size of 50 patients is hence required for the trial.

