### Statistical analysis

2.11

The analyses of the primary and secondary efficacy outcomes will be performed using the Full Analysis Set. Safety analysis will be conducted in the safety analysis population. For baseline characteristics, summary statistics will comprise frequencies and proportions for categorical variables, and means and SDs for continuous variables. The patient characteristics will be compared using Pearson *χ*^2^ test or Fisher exact test for categorical variables, and 1-way analysis of variance (ANOVA) for continuous variables.

For the primary analysis, to evaluate the responsiveness of FMA change to the daily total stimulus count of rPMS in chronic stroke patients with upper limb paralysis, the maximum contrast method will be performed with contrast coefficients (−1, 0, 1), (−1, −1, 2), and (−2, 1, 1). A change in the FMA score between Day 0 and Day 14, with the corresponding 95% confidence interval (CI), will be estimated for each group.

For the secondary analysis, Pearson *χ*^2^ test will be performed for categorical variables, and 1-way ANOVA for continuous variables. The significance level of the 2-sided hypothesis test is 5%, and the CI is a 2-sided 95% CI.

For the safety analysis, the frequencies of AEs will be compared using Pearson *χ*^2^ test or Fisher exact test, as appropriate.

All comparisons have been planned, and all *P* values will be 2-sided. *P* values < .05 will be considered statistically significant. All statistical analyses will be performed using SAS software, V.9.4 (SAS Institute, Cary, NC). The plan for statistical analysis was developed by the chief investigator and statisticians, and will be finalized before the database lock.

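### The stated safety analysis is an unordered significance test of AE frequencies in about 10/20/20 patients. It says little about moderate dose-related harm, and the muscle enzymes are not tied to it.

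*Protocol article*

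**What the plan says.** The Introduction makes safety an aim: "we aimed to assess the safety of rPMS therapy by comparing the incident rate of adverse events (AE) among groups". Section 2.11 (Statistical analysis) gives one sentence on method, a chi-square or Fisher exact test: "For the safety analysis, the frequencies of AEs will be compared using Pearson". It applies a two-sided 5% level to all comparisons. For the primary outcome the same section promises a 95% CI for the FMA change in each group. It names no estimate or interval specifically for AEs, and no period over which they are compared.

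Section 2.8 (Secondary outcomes) adds repeated blood tests with a safety purpose, in a sentence that begins: "To assess any muscular injury induced by rPMS therapy, laboratory tests for serum aspartate aminotransferase (AST), lactate dehydrogenase (LDH), and creatine kinase (CK) will be". These markers are not in the list of secondary outcomes that opens section 2.8, and the safety sentence in 2.11 does not mention them. Section 2.11 does give a general rule of 1-way ANOVA for continuous variables in the secondary analysis.

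The trial is sized on efficacy alone. Section 2.10 says that groups of 8, 16 and 16, before the allowance for dropout, "will provide an 80% power to detect differences of the change in FMA among the groups". Section 2.4 (Study procedure) states that control patients receive 4800 pulses of rPMS after the Day 14 evaluation.

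**The concern.** A significance test answers whether the data prove a difference in AEs. A safety aim needs the reverse: which differences the data still allow. With about 10 controls, a P value above .05 is the likely result even when AEs rise moderately with dose, and a P value alone does not show how large a difference remains possible. The test also ignores the order of the doses, although dose-response is the purpose of the trial.

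The enzymes are the safety data least exposed to open-label reporting, since patients and investigators know the allocation and investigators record the AEs. The article does not say how they enter the safety conclusion.

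The Discussion intends the chosen rPMS protocol to go forward to a larger double-blind trial, so what can be said about harm by dose matters for that step. An AE comparison over the whole study would also count patients as controls after they had started rPMS.

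**Working it through.** **Group sizes.** "The target sample size for this randomized trial is 50", allocated 1:2:2. So 50 × 1/5 = 10 controls and 50 × 2/5 = 20 in each rPMS group.

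**The plan's own figure.** I used the largest of the three stated contrasts with means 3.4/5.4/7.4, SD 3, two-sided 5%, and critical value and power by simulation. The 8/16/16 design has 83.4% power and 7/14/14 has 77.7%. So 8/16/16 is the smallest 1:2:2 size that reaches 80%, and 40/(1 − 0.20) = 50. The sample size is reproduced, but for FMA only.

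**Power of the AE test.** Let xⱼ be the number of patients with at least one AE in group j. Power is the sum, over all tables (x₁, x₂, x₃) with P < .05, of the product of the binomial probabilities Bin(xⱼ; nⱼ, pⱼ). The rates pⱼ are assumptions, because the article gives none.

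| Assumed AE rate, control/2400/4800 | Fisher, 10/20/20 | Pearson, 10/20/20 | Fisher, 8/16/16 |
|---|---|---|---|
| 0/10/20% | 10% | 16% | 6% |
| 0/15/30% | 29% | 32% | 16% |
| 10/20/40% | 34% | 37% | 23% |
| 0/20/40% | 57% | 57% | 34% |
| 0/25/50% | 82% | 82% | 57% |

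The lack of ordering costs power. At 5/15/30% with 10/20/20, the planned tests have 22% (Fisher) and 26% (Pearson), against 42% for an asymptotic trend test with scores 0, 1, 2.

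**A possible result.** Suppose AEs occur in 0/10, 3/20 and 6/20 patients. The pooled rate is 9/50 = 18%, so the expected counts are 1.8, 3.6 and 3.6. With e the expected count, each group contributes (x − e)²/e + (x − e)²/(n − e):
- control: 3.24/1.8 + 3.24/8.2 = 2.20
- 2400 pulses: 0.36/3.6 + 0.36/16.4 = 0.12
- 4800 pulses: 5.76/3.6 + 5.76/16.4 = 1.95

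The sum is 4.27 on 2 degrees of freedom, so P = exp(−4.27/2) = 0.12. The Fisher test gives P = 0.16. For 6/20 against 0/10 the difference is 30 percentage points, with a 95% interval from −1.8 to 51.9 (Newcombe, used here for illustration). The interval tells the reader far more than the P value.

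**Zero events.** The upper two-sided 95% limit is 1 − 0.025^(1/n). For n = 10 this is 30.8%, and for n = 20 it is 16.8%.

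**Enzymes.** Assume CK rises by factors of 1, 1.41 and 2 across the groups, with a between-patient log SD of 0.5. For within-patient log SDs of 0.3, 0.4 and 0.5, log CK adjusted for log baseline has about 98%, 88% and 73% power at 10/20/20. A 1-way ANOVA of the raw change has about 93%, 72% and 51%. All of these inputs are assumed, and so is the raw-change scale.

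**The case against.** Several objections are fair, and they limit the point.

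- **Markers.** A reader might infer that the enzymes go unanalysed. The article does not support that: they stand in section 2.8, and the general ANOVA rule may cover them. Their detailed tables may also sit in an analysis plan that is not shown. What stands is that the article does not tie them to the safety analysis, and that the one rule that might apply suits them poorly.
- **Interpretation.** A reader might infer that P > .05 will be reported as no difference or as safe. No section says so, and no equivalence claim is made. What stands is that a test is the only AE analysis the article names.
- **CK as an AE.** It is conjecture that a CK rise would count only if an investigator labelled it an AE, because the article gives no AE definition or laboratory criteria.
- **Power.** Low power for AEs is common to any trial of 50 sized on efficacy, and no reporting change raises it. That is a reason to present intervals rather than to rest on a test. Nor would real harm usually be missed whatever its size: at 10/20/20, power passes one half at 0/20/40% and reaches 82% at 0/25/50%.
- **CK figures.** Even raw-change ANOVA has 51–93% power for a doubling under the assumptions used. The gain from adjustment is real, but the simpler test is not useless.
- **Timing.** A comparison with control needs an exposure window, and the sampling days for the enzymes cannot be read because the content of Table 1 is not shown. The fix allows for both.

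**Conclusion.** The point holds in a limited form. Safety is a stated aim, yet its only stated analysis is an unordered test of AE frequencies with about 10–34% exact power for moderate dose-related harm at 10/20/20 (6–23% at 8/16/16). These figures rest on assumed AE rates, and the test becomes adequate only for large effects. A non-significant P value would therefore carry little information about moderate harm. The enzymes drawn for muscular injury are not explicitly assigned to the safety analysis, and a better method for them is available at almost no cost. Its advantage of roughly 5 to 22 percentage points (98 − 93 to 73 − 51) rests wholly on the assumed fold rises and SDs. The efficacy sample size is not in question.

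**What to change.** In section 2.11:

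1. **AEs.** For Day 0–14, before controls receive rPMS, report the proportion of patients with at least one AE per group, and each rPMS group's difference from control with an exact 95% CI. Base the safety statement on these intervals rather than on P > .05. Summarise AEs after Day 14 separately, by dose actually received.
2. **Enzymes.** Name CK, LDH and AST in the safety analysis. Analyse the log value at the last scheduled sample up to Day 14, adjusted for the log baseline value, and report each rPMS group against control as a ratio with a 95% CI.

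Both changes use data already to be collected, and section 2.11 says the analysis plan will be finalized before database lock. The cost is a few lines of wording, a little more analysis, and a safety conclusion that reads as less certain.

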### Secondary outcomes

2.8

The secondary outcomes in the present study are differences in spasticity, active ROM, motor evoked potential (MEP), and ADL during the study period. Differences in FMA scores between Day 0 and Day 28 and between Day 14 and Day 28 will be also analyzed. We will also evaluate the immediate changes of FMA score, active ROM, and MEP after the first session of rPMS therapy. Differences in FMA score, spasticity, active ROM, and ADL between day 28 and 4 weeks after discharge will also be analyzed.

Spasticity will be evaluated by using the modified Ashworth Scale (MAS), which is a 6-grade semiquantitative measurement used to assess the severity of spasticity.^[21]^ MAS scores for the shoulder, wrist, and finger flexors/extensors will be evaluated for each patient.

Active ROM goniometry will be evaluated for shoulder flexion/extension and abduction/adduction, elbow flexion/extension, hand flexion/extension, and finger flexion/extension. Subjects will be seated in a straight-backed chair and be must able to maintain this seated position for the duration of testing. Subjects will be instructed to make different movements of the joint while keeping the other upper extremity joints still, all the while seated and with the upper extremity hanging down.^[22]^

Moreover, to obtain electrophysiological measures of corticospinal integrity, the MEP amplitude induced by a single-pulse transcranial magnetic stimulation to the ipsilesional primary motor cortex will be recorded using a MagPro R30 magnetic stimulator and a figure-of-eight coil with a 70 mm radius (Magventure; Denmark). Because affected-arm MEPs could not be elicited at rest, we will determine the optimal coil position where a MEP will be elicited during the voluntary activation of triceps brachii.^[23]^ Eight stimulations will be performed with intensity set at 80% of maximum stimulator output and the averaged amplitude will be considered for statistical analysis.

The Functional Independence Measure (FIM) will be used for evaluating ADLs. FIM is a standardized and widely used tool for the assessment of ADLs, and its reliability and validity in the rehabilitation setting have been confirmed previously.^[24]^ The FIM includes 18 items rated on a 7-point scale, where the subtotal-summed scores of motor subscales (motor FIM) are used to quantify functional independence.

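### One P < .05 rule covers every secondary test as well as the primary, with no multiplicity control or exploratory status outside the primary maximum contrast test

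*Protocol article*

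**What the plan says.** In the protocol article, Statistical analysis (2.11), the primary analysis is one test on one outcome at one interval: "the maximum contrast method will be performed with contrast coefficients" for three dose-response shapes, applied to the Fugl-Meyer (FMA) change from Day 0 to Day 14. For the rest: "For the secondary analysis, Pearson *χ*^2^ test will be performed for categorical variables, and 1-way ANOVA for continuous variables". The level is the same throughout: "The significance level of the 2-sided hypothesis test is 5%, and the CI is a 2-sided 95% CI". The section closes by saying that the comparisons were all planned, that P values are two-sided, and that P "values < .05 will be considered statistically significant". It does not limit this last rule to the primary outcome.

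Secondary outcomes (2.8) lists what falls under the rule. The domains are "differences in spasticity, active ROM, motor evoked potential (MEP), and ADL during the study period". Spasticity is scored on the modified Ashworth Scale (MAS) by site: "MAS scores for the shoulder, wrist, and finger flexors/extensors will be evaluated for each patient". Range of motion (ROM) is recorded by joint and movement: "Active ROM goniometry will be evaluated for shoulder flexion/extension and abduction/adduction, elbow flexion/extension, hand flexion/extension, and finger flexion/extension". Further FMA intervals are added: "Differences in FMA scores between Day 0 and Day 28 and between Day 14 and Day 28 will be also analyzed". The section also plans analyses of the immediate change after the first session (FMA, ROM, motor evoked potential [MEP]) and of the change from Day 28 to four weeks after discharge (FMA, spasticity, ROM, activities of daily living).

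**The concern.** This is a rule the article states, not a detail it leaves out. It gives an isolated result on, say, one wrist movement the same label as the primary test. Each secondary test carries its own 5% error and nothing limits the error across them. Planning a test in advance protects against selective choice of analyses, but it does not change the error rate of a set of tests.

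What is at stake is how the secondary results are read. Ethics and dissemination (2.12) says that primary and secondary results will be published and reported to patients. The sample size section plans on only 8 evaluable controls. A single MAS or ROM result called statistically significant could be taken as evidence of a dose effect when it is one of many looks at the same arm.

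**Working it through.** **1. The plan's own figure, and what the primary test controls.** Inputs from Sample size estimation (2.10): mean changes 3.4, 5.4 and 7.4; SD 3; 8/16/16 evaluable patients; contrasts (−1, 0, 1), (−1, −1, 2), (−2, 1, 1); two-sided 5%. Simulation of the maximum contrast test (1,000,000 draws, pooled variance, 37 degrees of freedom) gives a joint critical value of |t| = 2.31 and power of 83.4%. With 7/14/14 the power is 77.7%, so 8/16/16 is the smallest 1:2:2 size that reaches 80%. For dropout, 40 / 0.8 = 50. The plan's figures reproduce. If the three contrasts were each tested at an unadjusted 5%, the error over the three would be 9.0%. The primary method removes that excess, and nothing comparable is stated for the secondary tests.

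**2. Counting the secondary tests.** The article gives no count, so this is an assumption built from Secondary outcomes (2.8). Let m be the number of MAS scores tested, r the number of ROM measures, and I the number of main intervals used for the four domains. I is taken as 1, 2 or 3, because the text says only that differences over the study period are of interest. Each endpoint gets one three-group test.

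- Main intervals: (m + r + 1 MEP + 1 Functional Independence Measure [FIM]) × I
- Extra FMA intervals: 2
- Immediate change: 1 FMA + r + 1 MEP = r + 2
- Day 28 to follow-up: 1 FMA + m + r + 1 FIM = m + r + 2

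Total k = (m + r + 2) × I + 2 + (r + 2) + (m + r + 2).

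**3. Expected false positives.** If no outcome is affected and each test holds its 5% level, the expected number is 0.05 × k. This holds whatever the correlation between tests.

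| Reading of 2.8 | m, r | k for I = 1, 2, 3 | 0.05 × k |
|---|---|---|---|
| One summary per domain | 1, 1 | 4I + 9 = 13, 17, 21 | 0.65, 0.85, 1.05 |
| Each site or movement pair once | 3, 5 | 10I + 19 = 29, 39, 49 | 1.45, 1.95, 2.45 |
| Every flexor/extensor score and direction | 6, 10 | 18I + 32 = 50, 68, 86 | 2.5, 3.4, 4.3 |

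Baseline and adverse-event comparisons fall under the same rule but are not counted here.

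**4. Chance of at least one false positive.** Without the correlations, this can only be bounded: it is at least 5% (the error of any one test) and at most the smaller of 1 and 0.05 × k. For k = 13 that is 5% to 65%. For k of 20 or more the upper bound is 100%. Treating the tests as independent would give 1 − 0.95^13 = 49%, 1 − 0.95^49 = 92% and 1 − 0.95^86 = 99%, but they are not independent. For any outcome, the Day 14-28 change is exactly the Day 0-28 change minus the Day 0-14 change, and the MAS, ROM and FMA measures describe the same limb in the same patients. The primary contrasts show the effect of correlation: independence would give 1 − 0.95^3 = 14.3% for three unadjusted tests, against the simulated 9.0%.

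**The case against.** The strongest reply is that this belongs to the statistical analysis plan. Only a condensed article is available, the plan is to be completed before the database is locked, and a .05 threshold is a conventional sentence. Unadjusted secondary tests are also common in a trial of 50 patients. Part of this stands: the unseen plan may label the secondary tests exploratory, and the article cannot be faulted for leaving a hierarchy to it. But the article does publish a significance rule without restriction, and an exploratory label elsewhere would have to qualify that rule.

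Four stronger readings are tempting, and the documents do not support them.

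- A reader might take 50 to 86 as the number of tests and conclude that several false effects are to be expected. Section 2.8 describes measurements, not a list of hypothesis tests, and names the Day 0-28 and Day 14-28 comparisons only for FMA. The coarsest reading gives about one expected false positive. It is also the least natural, because MAS and ROM are listed by joint and no summary score is named, but it is not excluded.
- A reader might infer that a spurious significant result is almost certain. That needs independence, which clearly fails here.
- A reader might take the remark that all comparisons were planned as the plan's argument for not adjusting. It stands beside the statement on two-sidedness and is not offered as a justification.
- A reader might infer that the primary result is compromised. It is not: one outcome at one interval is named, its contrasts are tested jointly, and no text lets a secondary result take its place. The Discussion itself calls for a larger double-blind trial to confirm the effect.

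**Conclusion.** The point holds as a matter of how secondary results will be labelled. The stated rule calls any secondary P below .05 statistically significant, and no error control or exploratory status is stated outside the primary test. Under the global null the expected number of false positives runs from 0.7 (13 tests) to 4.3 (86 tests). This range rests on the assumed splitting of MAS and ROM, on one to three main intervals, and on each test holding its 5% level. The probability of at least one false positive cannot be computed from the documents. The primary conclusion and the sample size are unaffected. The change is worth making before the analysis plan is finalized, but the trial's main claim does not depend on it.

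**What to change.** Amend the closing rule of Statistical analysis (2.11) to say that only the primary maximum contrast test on the Day 0 to Day 14 FMA change supports a claim of statistical significance. State that the secondary outcomes are exploratory and will be reported as estimates with 95% confidence intervals and nominal, unadjusted P values. Carry the same wording into the analysis plan.

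If a confirmatory secondary claim is wanted, name a short list in advance, either in a fixed order or with Holm adjustment, and test it only after a significant primary result. Which outcomes go on the list is the investigators' choice, and the list itself is optional.

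The cost is one or two sentences and fewer secondary claims. The sample size, data collection and primary test do not change.
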